### Statistical Analyses

Descriptive analyses will be conducted to examine whether randomization resulted in a balanced distribution of important demographic characteristics and the outcome variables in the two conditions. To control for potential bias, possible confounders will be included in all further analyses.

Analyses will be performed according to the intention-to-treat and completers-only principles, controlling for sex, age, and educational level. Intention-to-treat means that all participants will be analysed in the condition to which they were assigned by randomization. Therefore, missing data at follow up will be imputed using regression imputation. With respect to the completers-only analyses, only the participants with scores on all time points will be included, without the inclusion of imputed data. In both the intention-to-treat and the completers-only analyses, the effects of the intervention condition will be compared with those of the control condition. For continuous outcome measures, t-tests, or Man Whitney U if non-parametric distributions, will be performed. When correction for confounding variables is necessary, multivariate regression analyses will be performed. The fact that the data are clustered, because groups of respondents that are attending the same class and/or school are investigated, will be taken into account in the analyses.

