### Participants

#### Recruitment

A total of 100 schools were selected randomly from a list of all public secondary schools (N = 405) in four regions in the Netherlands (Zuid-Holland, Utrecht, Gelderland, Overijssel). Schools were invited to participate in the study, if the following inclusion criteria were met: 1. school had at least 600 students, 2. < 25% of students were from migrant populations, 3. school did not offer special education. A total of 15 schools were willing to participate and fulfilled the inclusion criteria. The main reasons for schools not participating were lack of time and no interest in participating in research in general.

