#### Randomization

Randomization occurred at the school level to avoid contamination between conditions. An independent statistician assigned the participating schools randomly to one of the two conditions: intervention or control. Randomization was carried out using a randomization scheme, stratified by level of education and school size, with the schools as units of randomization.

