### Data collection and instruments

The screening survey collected data by means of an online questionnaire on alcohol use, demographics, and personality risk factors. The data collection took place during a regular lesson (approximately 50 minutes), and questionnaires were administered by a research assistant from the Trimbos Institute. Those students randomly assigned to the experimental or control condition have completed, or will complete, the post-treatment survey after 2, 6, and 12 months. Data for the follow-up measurements have been, or will be, also collected online at school. The follow-up survey contains the same assessments as the screening survey. An overview of all measurements is given in Table 1.

**Table 1 T1:** Overview of measurements

Measurement	Baseline (screening)	Follow-up I (2 months after baseline)	Follow-up II (6 months after baseline)	Follow-up III (12 months after baseline)
Demographic characteristics	*	*	*	*
Truancy	*	*	*	*
Alcohol:				
Drinking behaviour	*	*	*	*
Drinking motives	*	*	*	*
Drinking problems	*	*	*	*
Perceived parental rules	*	*	*	*
Drinking parents	*	*	*	*
Tobacco:	*	*	*	*
Smoking behavior	*	*	*	*
Smoking parents	*	*	*	*
Perceived parental rules	*	*	*	*
Marijuana:	*	*	*	*
Marijuana-using behaviour	*	*	*	*
Marijuana parents	*	*	*	*
Other:	*	*	*	*
Personality	*	*	*	*
Anxiety	*	*	*	*
Psychological problems	*	*	*	*
Delinquency	*	*	*	*
Depression	*	*	*	*
Self control	*	*		

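### The baseline value of the outcome is not guaranteed in the model and school size is not listed; further adjustment appears to depend on an observed balance check, at a cost in precision and analyst discretion

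*Protocol article*

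**What the plan says.** All references are to the protocol article.

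- **Fixed covariates (Statistical Analyses).** The intention-to-treat and completers-only analyses are run "controlling for sex, age, and educational level".
- **Balance check (Statistical Analyses).** Descriptive analyses will "examine whether randomization resulted in a balanced distribution of important demographic characteristics and the outcome variables in the two conditions". The next sentence reads "To control for potential bias, possible confounders will be included in all further analyses". The confounders are not named, and no threshold or selection rule is given.
- **Choice of method (Statistical Analyses).** For continuous outcomes the named tests are the t-test or its rank-based alternative. Then: "When correction for confounding variables is necessary, multivariate regression analyses will be performed".
- **Stratification (Randomization).** Allocation was "stratified by level of education and school size, with the schools as units of randomization".
- **Baseline data (Data collection and instruments).** "The screening survey collected data by means of an online questionnaire on alcohol use, demographics, and personality risk factors", and "The follow-up survey contains the same assessments as the screening survey". Table 1 marks drinking behaviour and drinking problems at baseline and at all three follow-ups.
- **Number of clusters (Recruitment).** "A total of 15 schools were willing to participate and fulfilled the inclusion criteria".

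**The concern.** Baseline drinking is likely to be the best single predictor of later drinking, and it has already been measured. A plan that fixes sex, age and educational level but not the baseline outcome gives up precision that would cost nothing to collect. With 15 randomised units, precision is scarce.

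The order of the text also matters. Balance is examined, confounders are then included, and regression is used when correction is judged necessary. In a randomised trial that judgement can only come from the observed data, so the final model is not fixed. Balance between arms is also a poor guide to which covariates are worth having: a strongly prognostic variable improves precision even when it is perfectly balanced.

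The section is unclear within itself as well. It says the analyses control for three covariates, yet it names unadjusted two-sample tests as the starting point for continuous outcomes.

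The same section keeps one stratification factor (educational level) and does not list the other (school size). No reason is given.

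**Working it through.** **1. The plan's own figure.** Inputs from Sample size: 50% against 35%, two-sided alpha 0.05, power 0.80. The two-proportion formula gives 170 per condition without continuity correction and 183 with it, so the stated 183 reproduces. 183 × 1.4 = 256.2, which matches the stated 256. Nothing below changes these figures.

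**2. Inputs not in the documents.** The ICC (assumed 0.01 to 0.05) and the correlation r between baseline and 12-month outcome (assumed 0.3 to 0.6; up to 0.7 in step 5).

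**3. Power without baseline adjustment.** Mean school size in the trial is m = 512/15 = 34.1.

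- Design effect: DE = 1 + (m − 1) × ICC
- Effective n per arm: 256/DE
- SE = √[(0.50×0.50 + 0.35×0.65)/n_eff] = √(0.4775/n_eff)
- Noncentrality = 0.15/SE; power from the noncentral t with 15 − 2 = 13 df

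| ICC | DE | n_eff | Noncentrality | Power |
|---|---|---|---|---|
| 0.01 | 1.331 | 192.3 | 3.010 | 0.795 |
| 0.02 | 1.663 | 154.0 | 2.694 | 0.702 |
| 0.05 | 2.657 | 96.4 | 2.131 | 0.505 |

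Any gain from sex, age and educational level is ignored throughout.

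**4. Power with the baseline value in the model, ICC 0.02.**

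- Both variance components shrink equally: n_eff = 154.0/(1 − r²)
- Only the within-school part shrinks: n_eff = 256/[m × ICC + (1 − ICC)(1 − r²)]

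| r | Both: n_eff | Power, 13 df | Power, 11 df | Within only: n_eff | Power, 13 df | Power, 11 df |
|---|---|---|---|---|---|---|
| 0.3 | 169.2 | 0.742 | 0.730 | 162.6 | 0.726 | 0.713 |
| 0.5 | 205.3 | 0.820 | 0.808 | 180.6 | 0.769 | 0.757 |
| 0.6 | 240.6 | 0.875 | 0.865 | 195.4 | 0.801 | 0.789 |

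The 11 df columns show the cost of two school-level degrees of freedom: about one point. The factor 1 − r² is a linear-model result. For the yes/no binge item the gain depends on the correlation of the binary answers, which is unknown.

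**5. Does adjusting only after an observed imbalance recover the gain?** Simulation with 183 per arm, a continuous outcome, no clustering and the effect set for 80% power (4,000 runs; 10,000 under the null). Since the plan states no rule, a baseline difference at p < 0.05 was used as the trigger.

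| r | Power: never adjust | Power: always adjust | Power: adjust if imbalanced | Type I error: adjust if imbalanced |
|---|---|---|---|---|
| 0.3 | 79.1% | 82.8% | 79.6% | 4.9% |
| 0.5 | 79.6% | 90.0% | 81.1% | 4.2% |
| 0.7 | 80.8% | 98.1% | 82.4% | 3.9% |

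The trigger recovers little of the gain and does not inflate type I error.

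**6. School size.** Its effect on precision cannot be computed, because the documents give no between-school variance and no relation between school size and drinking.

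**The case against.** Baseline drinking is not excluded. The balance check expressly covers the outcome variables, so baseline drinking is among the candidates for later inclusion. A reader might infer that it has been left out; the text supports only that it is not guaranteed. The link between the check and the choice of covariates is itself read from neighbouring sentences, since no test or threshold is stated. Both points stand, and the claim is worded accordingly.

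A full covariate list is commonly left to an analysis plan that is not shown here. This has force for school size, about which the article is merely silent. It has less force for the rest: the article does state an adjustment set, and it does describe how further covariates come in.

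A reader might also infer that between-school variance dominates the standard error, so that baseline adjustment would transform power. The documents give no ICC to support this. The between-school share of the variance of a school mean is ICC/[ICC + (1 − ICC)/m]. At ICC 0.02 that is 0.02/(0.02 + 0.98/34.1) = 41%; it reaches 64% only at ICC 0.05.

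Finally, the gain may be small. At r = 0.3, with only within-school shrinkage and 11 df, power is 71% against 70% without baseline adjustment. That is correct, and it is why a range is given.

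**Conclusion.** The point holds as one of efficiency and pre-specification. The article fixes sex, age and educational level. It leaves the baseline outcome to what appears to be an imbalance-driven step, and it does not list school size.

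At an assumed ICC of 0.02, guaranteeing the baseline outcome would move power from about 70% to 73–80% (within-school shrinkage only) or 74–87% (equal shrinkage) for r of 0.3 to 0.6. The starting level itself runs from about 79% to 51% over ICC 0.01 to 0.05. All of this rests on assumed ICC and r, about 34 students per school, and a linear approximation to a binary outcome.

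It is tempting to conclude that choosing covariates by imbalance makes the test anti-conservative. That is not supported: under a fixed imbalance rule the simulated type I error was 3.9% to 4.9%. Free choice among unnamed confounders was not simulated, so the concern there is discretion, not a measured error rate. The school-size part is the lesser one and cannot be quantified.

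**What to change.** Name the covariates in advance for every analysis: the baseline value of the outcome (baseline binge status for binge drinking), sex, age, educational level and school size. Fit them in one regression model that accounts for clustering, and use it in place of two-sample tests with regression added when needed. Report baseline balance descriptively and do not use it to choose covariates. Label any adjustment prompted by an observed imbalance as a sensitivity analysis.

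No new data are needed: the student variables are in the screening survey, and school size was known at randomisation. The downside is that school size uses one or two of about 13 school-level degrees of freedom, roughly one point of power for two, in return for a gain that the documents do not allow to be estimated. If degrees of freedom are a worry, the baseline outcome is the part to secure first.

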### Sample size

#### Power

The power calculation reflects the idea that we want to induce a reduction in the percentage of students engaging in binge drinking (drinking five or more glasses of alcohol on one occasion) at least once during the last four weeks, from the current estimated 50% (among life-time users grade 9/10; estimate based on the results of a national school survey, [1]) to 35%. For a 15% reduction after 12 months among the students in grade 9/10, a sample size of N = 183 in each condition was required to test the hypothesis in a 2-sided test at alpha = 0.05 and a power of (1-beta) = 0.80. Because of the loss of power due to randomization of schools (and not students) and the increase in error because of applying a multiple imputation procedure to fill in missing values, 183*1.4 = 256 respondents per condition (intervention and control) needed to be included at baseline to test the effectiveness of the Dutch Preventure programme.

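### The sample size assumes multiple imputation, but the analysis section states only regression imputation for the intention-to-treat analysis, with no pooling; the two must be reconciled

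*Protocol article*

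**What the plan says.** The Power section of the protocol article starts from 183 students per condition and multiplies by 1.4 to reach 256. It gives two reasons for the factor: randomization by school, and "the increase in error because of applying a multiple imputation procedure to fill in missing values". It does not say how much of the 1.4 belongs to each.

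The Statistical Analyses section plans two analyses. The first is defined thus: "Intention-to-treat means that all participants will be analysed in the condition to which they were assigned by randomization". To keep everyone in, "missing data at follow up will be imputed using regression imputation". In the second, completers-only, "only the participants with scores on all time points will be included, without the inclusion of imputed data". The section then names t-tests, Mann-Whitney U tests and multivariate regression, and says that clustering by class and school will be allowed for. It does not say what enters the imputation model, whether one or several completed data sets are made, or how results would be combined. No expected rate of missing follow-up data appears in either section.

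**The concern.** The article states its method for missing data twice and names it differently each time. The version in the analysis section is the one an analyst would follow. Regression imputation, in its usual sense, puts each missing outcome at its predicted value, or at one draw around it, and analyses the result as if it had been observed. The full number of students is then counted, and nothing is added to the variance for not knowing the missing values. With prediction only, the residual variance also shrinks.

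The imputation touches every outcome in the intention-to-treat analysis at 2, 6 and 12 months. Depending on the imputation model, the cost is either confidence intervals that are too narrow or an effect that is too small. The allowance for imputation error built into the sample size would have no counterpart in the analysis. With two methods on record, the choice could also be made after results are seen.

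**Working it through.** **1. The plan's own figure.** The inputs from the Power section are binge drinking at 50% against 35%, "in a 2-sided test at alpha = 0.05 and a power of (1-beta) = 0.80".

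- Mean proportion: (0.50 + 0.35)/2 = 0.425.
- Without continuity correction: n = [1.960 × √(2 × 0.425 × 0.575) + 0.842 × √(0.50 × 0.50 + 0.35 × 0.65)]² / 0.15² = 169.3, so 170.
- With continuity correction: n' = (n/4) × [1 + √(1 + 4/(0.15n))]² = 182.4, so 183. This matches the plan.
- 183 × 1.4 = 256.2, given as 256. This also matches.

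The sample size therefore reproduces, and 256 is a figure that already allows for multiple imputation.

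**2. What single imputation does when condition is in the imputation model.** Let f be the fraction missing, completely at random, and let the imputation and analysis models hold the same terms. The estimated effect is then the observed-data estimate.

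- Its true standard error is σ√(2/(n(1−f))).
- The reported residual variance is about σ²(1−f), and all n per condition are counted, so the reported standard error is about σ√(1−f) × √(2/n).
- The ratio of reported to true is 1−f, so type I error is about 2Φ(−1.96(1−f)).

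Two simulations with 256 per condition, no true effect and no clustering agree with this. A used 5,000 runs and a covariate with R² 0.25. B used 3,000 runs, a binary outcome and a baseline covariate with latent correlation 0.5, and also ran multiple imputation with 10 imputations.

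| Assumed missing | Formula | A, predicted value | B, predicted value | A and B, one random draw | B, multiple imputation |
|---|---|---|---|---|---|
| 10% | 7.8% | 8.0% | 7.6% | 7.2%, 7.0% | 4.9% |
| 20% | 11.7% | 11.5% | 11.8% | 10.4%, 10.2% | 5.2% |
| 30% | 17.0% | 17.1% | 16.5% | 13.7%, 13.7% | 4.4% |

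Reported over true standard error for the predicted-value version in B was 0.89, 0.80 and 0.72. For multiple imputation it was 0.99 to 1.01. A continuous outcome at 20% missing gave 12.6% (predicted value), 11.1% (one draw) and 5.5% (multiple imputation).

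**3. Condition left out of the imputation model.** Imputed students then show no difference between conditions, so the estimate shrinks by about 1−f. The planned 15 points would become about 15 × 0.9 = 13.5, 15 × 0.8 = 12.0 and 15 × 0.7 = 10.5. Type I error for single imputation in B stayed at 4.6% to 6.1%. Multiple imputation without condition was conservative (2.9%, 2.0% and 0.9%), so moving to multiple imputation without naming condition would not be enough.

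**4. Allowing for clustering.** A further simulation used predicted-value imputation and a covariate-adjusted t-test on school means. Its assumptions were 15 schools split 8 and 7, about 256 per condition, a continuous outcome, covariate R² 0.25, intraclass correlation 0.01 to 0.05, 10% to 30% missing completely at random, and 3,000 runs.

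| Imputation model | Type I error |
|---|---|
| Condition in, school out | 7.1% to 15.6% |
| Condition omitted | 4.7% to 5.3% |
| School included | 4.4% to 5.9% |

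A school-level analysis does not by itself remove the inflation. Having school in the imputation model does.

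**The case against.** The best defence is that the two sections can be read together. Regression is a common engine inside multiple imputation, so the Power section could be giving the framework and the analysis section the model. The word single does not appear in the article. On that reading the standard errors are valid and one clarifying phrase is enough. This stands as a possibility, but the analysis section gives no sign of it: there is no mention of several data sets or pooling, and a Mann-Whitney U test has no standard pooled form under Rubin's rules. Either reading leads to the same edit.

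A reader might infer more: that the plan as written makes the intention-to-treat standard errors too small and raises false positives. The document does not support that as a general statement. The inflation needs single imputation, condition in the imputation model and school out of it, and the article fixes none of these. The size also depends on attrition that is nowhere stated. The 93% class attendance used for the survey sample is not a 12-month retention rate.

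Nor may one infer that intention-to-treat is the main analysis, because the section lists it beside completers-only without ranking them. The completers-only analysis uses no imputed data and is untouched. It drops everyone with a missing wave, however, and so cannot stand in for the comparison of all students as randomized.

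Finally, much imputation detail properly belongs in the statistical analysis plan, which is not shown. That excuses an unstated number of imputations. It does not excuse naming two different methods.

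**Conclusion.** The point holds as an unreconciled difference between the Power and Statistical Analyses sections, with a conditional consequence. On the ordinary reading of the analysis section, imputation uncertainty is ignored. What follows depends on an imputation model that the article does not state:

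- **Condition in, school out:** type I error of about 7-8%, 10-12% and 15-17% at 10%, 20% and 30% missing. One random draw instead of the predicted value gives about 7%, 10% and 14%.
- **Condition omitted:** type I error near 5%, and the effect pulled towards zero by roughly the missing fraction.
- **School included and analysis at school level:** type I error near 5%.

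All figures assume data missing completely at random, and the 10% to 30% range is an assumption. The figures show why the wording matters; they do not predict this trial's error rate.

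**What to change.** In the Statistical Analyses section, replace regression imputation with multiple imputation, as the Power section already assumes. State that:

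- the imputation model contains condition, school, baseline outcome and the analysis covariates (school can enter as a random effect, since condition does not vary within a school);
- binary outcomes such as binge drinking are imputed with a model suited to them, for example logistic;
- results are pooled by Rubin's rules.

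A mixed model fitted to all observed waves, without imputation, is an acceptable alternative. If regression was always meant as the engine of a multiple imputation, the same sentence settles it. The number of imputations and the full predictor list can be left to the statistical analysis plan.

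The sample size stays at 256 per condition. The cost is a change of wording, a little computing and slightly wider confidence intervals.

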The four personality profiles were subsequently found to be strongly related to adolescents' quantity and frequency of drinking, frequency of binge drinking, and severity of alcohol problems [25,26]. Each personality profile is associated with specific substance misuse patterns, maladaptive motives for use, and vulnerability to specific forms of co-morbid psychopathology in adolescents [27,28]. Impulsivity is related to an increased risk of the early onset of alcohol and drug problems [29]. Sensation seekers drink more [30], tend to drink in order to enhance euphoric (intoxicating) effects [28], and are more at risk of adverse drinking outcomes (e.g. [30]). Highly anxiety sensitive persons show increased levels of drinking [31], are more responsive to the anxiety-reducing effect of alcohol, and are more likely to use alcohol to cope with negative feelings [28]. Persons with high levels of hopelessness often have depression-specific motives for alcohol use [32] and usually drink to cope with negative feelings [16,28,33,34].

The Preventure programme screens a school population for pupils who already drink alcohol and, additionally, belong to one of the four high-risk personality profiles. The programme identifies and treats high-risk adolescents, with the aim of preventing or intervening early before the high-risk adolescents engage in risky behaviours and/or these behaviours become problematic. The selected pupils are offered a tailored intervention based on cognitive behaviour therapy (CBT) and motivational interviewing. Cognitive behavioural techniques are used to target maladaptive thinking and coping skill deficits, and motivational interviewing techniques are used to address motivation to take responsibility for one's problematic behaviours. Motivational interviewing has proven to be effective for alcohol- and drug-related behaviour, and CBT can lead to reduction in anxiety sensitivity, depressive cognitions, and impulsivity (e.g. [35,36]). The manualized intervention, developed by [name] and colleagues [35], provides personalized feedback and personality-specific cognitive-behavioural exercises designed to facilitate more adaptive coping. The focus is not on drinking (or drug use) per se but on risky ways of coping with personality, such as avoidance, distraction, and aggressive thinking, that may lead to substance misuse or other risky behaviour.

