### Aims and hypotheses

In 2009, a project was started to develop and test Preventure in the Netherlands, where currently there is no selective school-based alcohol prevention available [37]. The main objective of this project is to study the effectiveness of Preventure on drinking behaviour of young adolescents in secondary education in the Netherlands. The effectiveness of the Dutch Preventure is being assessed by conducting a clustered randomized controlled trial (RCT), with two conditions (treatment and control arms). This is the first time that Preventure has been studied outside the setting where it was developed, England and Canada, to prove its effectiveness outside this setting.

The most relevant outcomes are percentage reductions in binge drinking (≥ five drinks on one occasion in the past four weeks), weekly drinking, and drinking-related problems after 2, 6, and 12 months. The main hypothesis is that high-risk students who receive the personality targeted intervention will score lower on these outcomes relative to those in the no-treatment control group. In addition, our secondary aim is to test the effects of the programme on emotional and behavioural problems (e.g. aggression, truancy, and shoplifting). Our hypothesis is that Preventure facilitates lower depression rates, lower anxiety rates, lower delinquent behaviour rates, less problem behaviour, and lower truancy.

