#### Intervention condition

The intervention involved two group sessions, carried out at the participants' schools. The group sessions were adapted to one of the four personality profiles. This means that there were four different groups of two sessions each. Both group sessions lasted 90 minutes and were spread across two weeks. The intervention was provided by a qualified counsellor and a co-facilitator. The three counsellors and two co-facilitators had received two days training from [name], who developed the original intervention. Furthermore, all the counsellors had practiced the two group sessions at a pilot school with students who met the inclusion criteria (drinkers with high-risk personality profiles).

The intervention used student manuals. The original student manuals, developed in Canada, were translated and adapted to the cultural and school context of the Netherlands. The examples, the real-life stories, and the illustrations used in the programme manuals were adapted to the Dutch situation. The student manuals consist of text, exercises, and real-life experiences or scenarios. The real-life scenarios were generated by previously organized focus groups of high-risk personality adolescents. In four focus groups (one group for each personality risk factor), students were asked to share their own experiences regarding, for example, alcohol and drugs. The student manuals had been tested during the pilot sessions at the pilot school. Students were asked to give their opinion on the content, the illustrations, and real-life stories used in the manuals.

In the first group session, psycho-educational strategies were used to educate students about the target personality variable (NT, AS, IMP, or SS) and the associated problematic coping behaviours, such as interpersonal dependence, aggression, risky behaviours, and substance misuse. Students were motivated to explore their personality and ways of coping with their personality through a goal-setting exercise. Thereafter, they were introduced to the cognitive behavioural model by analysing a personal experience according to the physical, cognitive, and behavioural responses.

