As already mentioned, the SURPS [25] distinguishes four personality profiles. Each profile is assessed using five to seven items that could be answered on a 4-point scale, 1 = *strongly disagree*, 2 = *disagree*, 3 = *agree*, 4 = *strongly agree*. The SURPS scale has 23 non-overlapping items that assist in discriminating personality dimensions independent of substance use behaviour. Negative Thinking (7 items) refers to hopelessness, which might lead to depressive symptoms. A sample item on the Negative Thinking subscale is 'I feel that I'm a failure.' The Anxiety Sensitivity dimension (5 items) measures fear of bodily sensations, and an example item is 'It frightens me when I feel my heart beat change.' The Sensation Seeking subscale (6 items) measures the tendency to seek out thrilling experiences, e.g. 'I would like to learn how to drive a motorcycle.' The tendency to act without thinking is measured by the Impulsivity subscale (5 items), and an example of this subscale is 'I often don't think things through before I speak.' Studies in both adolescent and adult samples in several countries, including the Netherlands, have shown that this scale has good internal reliability, good convergent and discriminant validity, and adequate test-retest reliability [34,40,41,25,27]. The instrument was translated into Dutch by an English speaking language consultant, has been successfully applied [34], and was tested at schools before use in the screening survey.

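### The stated covariates omit personality profile, the screening variable that decides which sessions a student receives; keep the pooled comparison, adjust for profile, and prespecify two profile-matched supportive estimates

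*Protocol article*

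**What the plan says.** The Eligibility section places each high-risk student in exactly one of four profiles, using the largest z-score on the screening scale, in all 15 schools. Profile is therefore a baseline variable known in both arms. The Intervention condition section says that the sessions were adapted to the profile: "This means that there were four different groups of two sessions each".

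The Preventure section reports that the profiles are strongly related to how much and how often adolescents drink. It adds: "Each personality profile is associated with specific substance misuse patterns, maladaptive motives for use, and vulnerability to specific forms of co-morbid psychopathology in adolescents". Under Data collection and instruments the link to one outcome is explicit: "Negative Thinking (7 items) refers to hopelessness, which might lead to depressive symptoms". The same section describes Anxiety Sensitivity as fear of bodily sensations, and the Outcomes section describes the CASI as measuring fear of anxiety symptoms.

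The secondary hypothesis under Aims and hypotheses is stated for the programme as a whole: "Our hypothesis is that Preventure facilitates lower depression rates, lower anxiety rates, lower delinquent behaviour rates, less problem behaviour, and lower truancy".

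Under Statistical Analyses the planned contrast is: "In both the intention-to-treat and the completers-only analyses, the effects of the intervention condition will be compared with those of the control condition". The named covariates are sex, age and educational level. Unspecified possible confounders are to be added as well. Profile is not mentioned in that section.

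**The concern.** The article commits itself to a short covariate list and passes over a variable that its own background marks as prognostic. Two things follow.

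First, schools were randomised, only 15 of them, so the profile mix can differ between arms by chance. If it does, and profile predicts the outcome, the unadjusted difference carries an error equal to the difference in profile shares multiplied by the difference in outcome between profiles. Adjustment removes this and may also improve precision. The documents give no figure for how much outcome variation profile explains, so the gain cannot be sized.

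Second, depression and anxiety are each tied by the article to a particular profile. If the benefit on CES-D or CASI were concentrated in the matching profile, the pooled estimate would average it with students who attended another version, and the plan names no estimate that would show it.

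**Working it through.** **Inputs from the protocol article.** The Power section uses a "2-sided test at alpha = 0.05 and a power of (1-beta) = 0.80", binge drinking falling from 50% to 35%, and states that "a sample size of N = 183 in each condition was required". A factor of 1.4, for school randomisation and imputation, gives 256 per arm.

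**Reproducing the plan's figure.** The two-proportion formula with pooled variance under the null gives 170 per arm, or 183 with continuity correction, which matches. 183 × 1.4 = 256.2. There is no arithmetic error. The calculation is for all profiles together.

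**Effective numbers.** Undoing the article's discount, 256 students per arm count as 183. A profile with share s has 183 × s per arm.

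**Assumptions.** The profile mix is not stated, so s = 25% is used, with a range of 15% to 40%. The effect is a standardised difference d in one profile and zero in the other three.

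**Formulas.** The pooled effect is s × d. Power is Φ(effect / √(2/n) − 1.96), ignoring the negligible opposite tail.

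For s = 25%, d = 0.5:
- Pooled: effect 0.25 × 0.5 = 0.125; √(2/183) = 0.1045; 0.125/0.1045 = 1.196; power 22%.
- Matched profile: n = 45.75; √(2/45.75) = 0.2091; 0.5/0.2091 = 2.391; power 67%.

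| Share s | d in profile | Pooled d | Power, pooled | Power, matched profile |
|---|---|---|---|---|
| 15% | 0.5 | 0.075 | 11% | 46% |
| 25% | 0.3 | 0.075 | 11% | 30% |
| 25% | 0.5 | 0.125 | 22% | 67% |
| 25% | 0.6 | 0.150 | 30% | 82% |
| 40% | 0.5 | 0.200 | 48% | 86% |

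**Opposite case.** With a uniform d = 0.25, the pooled ratio is 0.25/0.1045 = 2.391 (67% power) and the single-profile ratio is 0.25/0.2091 = 1.196 (22%). The ranking reverses.

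**Break-even.** Let the other profiles show a fraction r of the matched effect. The two tests have equal power when s + (1 − s)r = √s, so r = √s/(1 + √s). At s = 25%, r = 0.5/1.5 = 1/3; at 15%, 0.28; at 40%, 0.39. If the other profiles show more than about a third of the effect, pooling is the stronger test.

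**Binge drinking by profile (four equal profiles, 45.75 per arm each).**
- Power for a 15-point effect within one profile is 30% (20% to 45% for shares of 15% to 40%).
- The 95% half-width is 1.96 × √((0.25 + 0.2275)/45.75) = 0.20, or 20 points. With 64 per arm and no discount it is 17 points.
- Suppose one version has no effect and the other three give 15 points. The 1 df interaction has standard error √(0.5/45.75 + 0.4775/137.25) = 0.120, and 0.15/0.120 = 1.25 gives 24% power. A 3 df heterogeneity test has 16%.
- Four unadjusted profile tests, taken as independent, carry a familywise error of 1 − 0.95⁴ = 18.5%.

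**The case against.** The strongest reply is that nothing here is wrong. The main objective, the secondary hypothesis, the two-arm design and the power calculation all concern the programme, meaning screening plus a tailored version, and the pooled contrast answers that question. This stands: pooling is the correct main analysis. Subgroup analyses are also commonly left to an analysis plan that is not shown, so their absence from an article is no fault in itself. The article further promises to include possible confounders, and profile could be one. That last reply is only partial. The balance check it describes covers demographic characteristics and outcome variables, so entry of profile is possible but not assured.

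A reader might go further than the documents allow in four ways.

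- **That depression and anxiety are each targeted in only one profile.** No section says so. All versions share three components (Theoretical basis), students high on several scales sit in a single group (Eligibility), and earlier emotional effects are reported without restriction to a profile (Preventure). Any spill-over lessens the dilution.
- **That the planned analysis hides a version that does not work.** A pooled test cannot show this, but at this size a profile-level analysis would rarely show it either (16-24% power for heterogeneity).
- **That roll-out claims should be made version by version.** Requiring significance in each profile would fail a fully effective version about 70% of the time (100% − 30%), letting imprecise estimates override the powered comparison.
- **That the power gap is 29% against 81%.** This treats all 256 per arm as independent, which the article itself does not do.

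**Conclusion.** The point holds as a modest improvement to the stated model. The main comparison is sound and should stay. The covariate list should include profile, which is already collected, precedes the sessions, and is described by the article as related to drinking and to particular psychopathology.

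The case for two matched supportive estimates is conditional. If an effect of d = 0.5 were confined to one profile of about 25%, pooled power would be about 22% (11-48%) against 67% (46-86%) in that profile. This rests on an assumed profile share of 15-40%, no effect elsewhere, and 183 effective students per arm. If the other profiles show more than about a third of the effect (at a 25% share), the advantage passes to the pooled test. The matched estimates therefore belong beside the pooled one and not in its place.

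**What to change.** In the Statistical Analyses section:

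1. Add personality profile (four categories, as assigned at screening) as a fixed covariate in all outcome models, next to sex, age and educational level. Simple two-group tests cannot carry it, so this uses the regression route that the section already provides, with the clustering handled as planned.
2. Keep the pooled intervention-control estimate as the main result for every outcome.
3. Prespecify two secondary, supportive estimates with confidence intervals: CES-D within Negative Thinking and CASI within Anxiety Sensitivity, each shown beside its pooled estimate.
4. Report binge-drinking estimates by profile with confidence intervals, labelled exploratory, with no decision rule attached.

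This changes wording only and needs no new data. The price is three model parameters and a few imprecise estimates. At a 25% share the half-width is about 1.96 × 0.2091 = 0.41 standard deviations for CES-D or CASI, and 17 to 20 points for binge drinking. Fixing the two matched estimates before the outcome data are analysed keeps them apart from a search through subgroups.
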